### Measures: baseline and outcome and process measures

The clinical pilot and public pilot are different interventions with shared metrics and also exclusive ones to each case. The primary outcome, the smoking cessation rates, will be measured at the 60, 120, and 180-day follow-up time points, using the urinary cotinine and expired carbon monoxide levels in the clinical pilot case, and the self-reported questionnaires in the public pilot case. To assess the secondary outcomes, different metrics are required. Table 2 includes information about how they will be calculated, to which other metrics they will be compared, and to which pilot they are related.

**Table 2 Tab2:** Description of metrics to assess the primary and secondary outcome

Metric	Calculation	Comparisons	Pilot	Related secondary outcome
Primary outcome				
Smoking cessation rate	Total number of people who relapsed / total number of people in the group at 60 days, 120 days, and 180 days of their quitting date	• User engagement at an individual level • User engagement at an aggregated level • User mobile app usage • User quitting attempts • User lifestyle feedback • Physical activity	• Clinical • Public	System influence on smoking cessation and app influence on users physical activity levels
Secondary outcomes				
User engagement at an individual level	Messages read by the user / total number of messages sent to the user	• Smoking cessation rate	• Public • Clinical	System influence on smoking cessation
Engagement at an aggregated level	Mobile application rolling retention, session length distribution, session frequency, sessions per user, return rate	• Smoking cessation rate	• Public • Clinical	System influence on. smoking cessation.
User quitting attempts	Number and date of quitting attempts	• Smoking cessation rate	• Public • Clinical	System influence on smoking cessation
User app behavior	Time spent per app section	• User message ratings • User satisfaction with messages	• Public • Clinical	App usage. and opinions on messages the users received
User satisfaction with messages	Satisfaction questionnaire	• User mobile app usage • Mobile app behavior • User message ratings	• Clinical	App usage and opinions on messages the users received
User message ratings	Users’ votes for each message on a 5-star scale	• User app behavior	• Public • Clinical	App usage and opinions on messages the users received

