### Statistical analysis

In the clinical pilot, patients will be classified as either smokers or non-smokers according to their positive or negative values in the urine test and the expired CO tests (PiCO values between 0 and 6 will be considered non-smokers) at each follow-up visit. In case of discrepancy between tests, we will consider the patient as a smoker. We will perform repeated analysis of variance (ANOVA), and provide *p* values, to compare the number of non-smokers in the intervention versus control group at 2 months, 4 months and 6 months of their quitting day.

In the public pilot, users will be considered to be non-smokers according to their self-reported answer to the question: “Are you still resisting the temptation or have you smoked? Please, be honest.” We will perform repeated ANOVA, and provide *p* values, to compare the number of non-smokers in the intervention versus control group every 2 weeks.

For secondary outcomes, the numerical variables (user engagement at aggregated level, user mobile app usage, user quitting attempt, user app behavior, and user lifestyle feedback EuroQoL 5 dimensions 5 levels questionnaire (EQ-5D-5 L) and Short Form 36-item Health Survey (SF-36), and physical activity) will be assessed with *T* tests and variance ANOVA tests. Categorical variables (user engagement at individual level, user satisfaction with messages, user message ratings, and lifestyle answers to the International Physical Activity Questionnaire (IPAQ)) will be assessed with chi-square tests. In addition, we intend to study the combination of all metrics with a linear regression analysis, and the Kaplan-Meier method to analyze the overall survival rate (non-smokers). All tests will be two-tailed and with a significance level set at 0.05. All analyses will be done according the intention-to-treat principle, and using the SPSS software version 25. Missing data will be calculated with the last observation carried forward.

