### Sample size and power calculations

Calculations regarding the needed number of participants to measure the primary outcome – smoking cessation rates – have been done to ensure the statistical significance of the results.

For the clinical pilot, accepting an alpha risk of 0.05 and a beta risk of 0.2 in a two-sided test, 45 subjects will be necessary in both the first group and second groups in order to find a statistically significant proportion difference, which is expected to be 0.2 and 0.5 in the first and second groups, respectively.

For the public pilot, accepting an alpha risk of 0.05 and a beta risk of 0.2 in a two-sided test, 489 subjects are necessary in first group and 489 in the second to find as statistically significant a proportion difference, expected to be of 0.07 in group 1 and 0.14 in group 2.

A dropout rate of 15 and 20% is anticipated for the clinical and public pilot, respectively. Although other studies using computer-tailored interventions have reported higher dropout rates, this study will consider participants who do not return for the consultation at month 6 to be failure cases. Consequently, the anticipated dropout rates include only those who withdraw for reasons other than relapse.

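### The yes/no cessation outcome is analysed with repeated ANOVA over several visits and no decisive time point or test is named, although each pilot is sized on one difference in proportions

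*Protocol article*

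**What the plan says.** - **Outcome.** Under Statistical analysis, each participant is a smoker or a non-smoker at each assessment: by urine and CO tests in the clinical pilot, by self-report in the public pilot.
- **Method.** For the clinical pilot, "We will perform repeated analysis of variance (ANOVA"), with p values, at 2, 4 and 6 months. The same method is used in the public pilot, "to compare the number of non-smokers in the intervention versus control group every 2 weeks".
- **Schedule elsewhere.** The Measures section says of the primary outcome in both pilots that it "will be measured at the 60, 120, and 180-day follow-up time points".
- **Significance level.** "All tests will be two-tailed and with a significance level set at 0.05". No adjustment is stated, and no visit or test is named as the one that decides.
- **Sample size.** The clinical pilot needs 45 per group "in order to find a statistically significant proportion difference", with rates "expected to be 0.2 and 0.5 in the first and second groups, respectively". The public pilot needs 489 per group for 0.07 against 0.14. No time point is attached to these rates. Month 6 appears in that section only in the rule that those who miss that consultation count as failures.

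**The concern.** The plan sizes one contrast and analyses another. In a repeated ANOVA the group effect compares each person's status averaged over all visits, and the group-by-time effect asks whether the curves differ in shape. Neither is the difference in proportions at a single time. A trial of cessation could then be declared positive on an early difference that has vanished by the end of follow-up, or could miss a difference that appears late.

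The text also leaves open which p value counts. It promises p values at three visits or at every two-week assessment, each at 0.05. If several are read, false positives accumulate. In the public pilot the two sections do not even agree on how many occasions there are.

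**Working it through.** **1. What the trial was sized for.** Inputs from Sample size and power calculations: alpha 0.05 two-sided, power 0.80, rates 0.2 v 0.5 and 0.07 v 0.14. With pooled variance, n = [1.96√(2p̄q̄) + 0.842√(p1q1 + p2q2)]² / d².
- Clinical: p̄ = 0.35, d = 0.3. n = (1.322 + 0.539)² / 0.09 = 38.5, so 39; with continuity correction 45. The stated 45 is reproduced.
- Public: p̄ = 0.105, d = 0.07. n = (0.850 + 0.362)² / 0.0049 = 299.9, so 300; with continuity correction 328. The stated 489 is not reproduced; it gives power 0.948. That is a separate point, and because the figure errs on the large side it does not affect this one.

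Both calculations are for one comparison of two proportions, with no term for repeated measures or multiplicity.

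**2. Number of occasions.** Clinical: 3. Public: 180/14 = 12.9, so 12 to 13 under Statistical analysis, against 3 under Measures.

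**3. What the group effect tests.** The documents give no abstinence curves, so those below are assumptions. Relapse is taken as permanent, with 50 or 500 per arm.

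Early effect only, no difference at 6 months:
- Clinical, 0.40/0.24/0.20 v 0.60/0.34/0.20. Visit averages are 0.28 v 0.38, a difference of 0.10, while the 6-month difference is 0. The group test is significant in about 25% of runs.
- Public, 12 points, control falling from 0.73 to 0.07, intervention from 0.87 to 0.07. The averages (2.98/12 = 0.248 v 3.81/12 = 0.318) differ by about 0.07, while the 6-month difference is 0. The group test is significant in about 96% of runs, and in 98% under another curve (60% falling to 7% over 13 points).
- The 6-month test stays at about 5% in both pilots.

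**4. Power when the sized difference is present at 6 months.**

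| Pilot and assumed pattern | Averaged group test | Direct 6-month test |
|---|---|---|
| Public, curves separate late | 0.17 | 0.95 |
| Public, gradual separation | 0.82 | 0.95 |
| Public, 60% falling to 7% v 14% | 0.86 | 0.95 |
| Clinical, 50/32/20% v 60/55/50% | 0.65-0.68 | 0.89 |
| Clinical, late (40/24/20% v 50/50/50%) | 0.67 | 0.90 |
| Clinical, 40/24/20% v 62/53/50% | 0.86 | 0.89 |
| Clinical, 30/25/20% v 60/55/50% | 0.90-0.91 | 0.89 |

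**5. False positives with no effect.**
- One pre-named group test: 0.052 to 0.054 in simulation.
- Each time point read at 0.05, independent visits: 1 − 0.95³ = 0.143; 1 − 0.95¹² = 0.460; 1 − 0.95¹³ = 0.487.
- Correlated test statistics (correlation 0.95 down to 0.5): about 0.07 to 0.13 for three visits and 0.11 to 0.43 for 12 to 13.
- Permanent relapse, simulated: about 0.10 to 0.12 (clinical) and 0.25 (public).

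**6. After the fix.** Power = Φ{[d√n − 1.96√(2p̄q̄)] / √(p1q1 + p2q2)}.
- Clinical, 50 per arm: Φ[(2.121 − 1.322)/0.640] = 0.894.
- Public, 500 per arm: Φ[(1.565 − 0.850)/0.431] = 0.952.
- After the stated dropout of 15% (42 per arm) and 20% (400 per arm): 0.834 and 0.899.
- Keeping every time point with Bonferroni would instead need 52 (3 tests) or 526 to 533 (12 to 13 tests) per arm before dropout, above the planned 50 and 500.

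**The case against.** Four stronger readings are tempting, and the documents support none of them outright.

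- **That repeated ANOVA in itself inflates type I error here.** It does not: with equal arms a single group test holds about 5% even on 0/1 data. The analysis sentence can be read as one such test per pilot. Inflation arises only if several p values are each read at 0.05, which the wording permits but does not require.
- **That non-sphericity spoils the analysis.** An uncorrected group-by-time test in the public pilot has a simulated error of about 14-15%, but with a Greenhouse-Geisser correction 0.054, and with three clinical visits even the uncorrected test gives 0.054-0.056. The article does not say that the correction is omitted, and an analysis plan may specify it.
- **That power is necessarily lost.** It depends on the curve. In the clinical pilot the loss can disappear, and in the public pilot two of the three assumed patterns still exceed the planned 80%.
- **That the plan states a 6-month difference.** It does not. Month 6 is inferred from the 6-month follow-up and the month-6 failure rule.

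The early-only scenario is also deliberately unfavourable, and its effect is far smaller in the clinical pilot (about 25%) than in the public one.

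These objections make the sizes conditional. They do not remove the mismatch between the sized contrast and the analysed one, the missing decisive time point, or the conflict over the public schedule. Nor is this detail that an article may leave to an analysis plan: the article itself fixes the method, the times and the 0.05 level.

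**Conclusion.** The point holds. As written, the primary analysis does not target the single difference in proportions that each pilot was sized on, and nothing says which time point or test decides. The most serious consequence is a positive result with no difference left at 6 months. False-positive inflation is conditional on reading several p values and depends on an unknown between-visit correlation. Loss of power is a possibility whose size, from severe to none, depends on the shape of the abstinence curves. All simulated figures rest on assumed curves and should be read as ranges. Taking 6 months as the sized time point is an inference.

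**What to change.** 1. In both pilots, name day 180 as the single primary time point.
2. Compare the proportion of non-smokers among all randomised with a two-proportion test or logistic regression. Report the risk difference with its 95% CI, at two-sided 0.05.
3. Treat the 60-day, 120-day and two-weekly data as secondary, in a GEE or mixed logistic model, without confirmatory claims.
4. Reconcile the public-pilot schedule between Measures (60, 120, 180 days) and Statistical analysis (two-weekly).
5. State one origin for day 180. Table 2 and Statistical analysis count from the quitting date; Materials counts from the initial consultation.
6. State one rule for missing month-6 status. Statistical analysis carries the last observation forward; the sample size section counts non-returners as failures. The primary proportion depends on which applies.

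Covariate adjustment is optional and not needed to cure the fault. The cost is rewording the analysis paragraph and aligning these sections. No additional data or participants are needed.

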## Abstract

**Background:**

Smoking cessation is the most common preventative for an array of diseases, including lung cancer and chronic obstructive pulmonary disease. Although there are many efforts advocating for smoking cessation, smoking is still highly prevalent. For instance, in the USA in 2015, 50% of all smokers attempted to quit smoking, and only 5–7% of them succeeded – with slight deviation depending on external assistance. Previous studies show that computer-tailored messages which support smoking abstinence are effective. The combination of health recommender systems and behavioral-change theories is becoming increasingly popular in computer-tailoring. The objective of this study is to evaluate patients’s smoking cessation rates by means of two randomized controlled trials using computer-tailored motivational messages. A group of 100 patients will be recruited in medical centers in Taiwan (50 patients in the intervention group, and 50 patients in the control group), and a group of 1000 patients will be recruited on-line (500 patients in the intervention group, and 500 patients in the control group). The collected data will be made available to the public in an open-source data portal.

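### Individual engagement is defined as a per-user proportion, but the analysis section lists it as categorical and assigns a chi-square test that does not fit it

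*Protocol article*

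**What the plan says.** Table 2 (Measures: baseline and outcome and process measures) calculates engagement at the individual level as "Messages read by the user / total number of messages sent to the user". The one comparison it lists for this metric is with the smoking cessation rate, in both pilots.

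The Statistical analysis section divides the secondary outcomes into two lists:

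- **Numerical.** Aggregated engagement, app usage and app behaviour are among the variables that "will be assessed with *T* tests and variance ANOVA tests".
- **Categorical.** This list opens "Categorical variables (user engagement at individual level, user satisfaction with messages, user message ratings" and its members "will be assessed with chi-square tests".

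The common rule is: "All tests will be two-tailed and with a significance level set at 0.05". The section also plans a linear regression that combines all metrics. Nothing in the article gives cut-points for the engagement ratio.

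Table 1 gives the app to both public arms but only to the intervention arm of the clinical pilot. The Discussion names higher engagement, individual and aggregate, as an expected result.

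**The concern.** A chi-square test needs a table of counts. A read/sent ratio supplies one only after a further decision: band the ratio, treat each observed value as its own category, or set the users aside and count messages. The article makes none of these decisions, and the three routes behave very differently. If the choice is made once data are in hand, the result depends on it.

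This metric is meant to show the system's influence on cessation, so its analysis should use the information in the ratio. A test that discards the ordering of the values can miss a relation with cessation that a numerical analysis would detect. A test that ignores the clustering of messages within users can report one that is not there.

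**Working it through.** **Passages side by side.** Table 2 gives a per-user proportion. The analysis section gives a categorical label and a chi-square test. The neighbouring app metrics (aggregated engagement, time spent per app section) are in the numerical list. The mismatch is in the text and needs no calculation.

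**Figure to reproduce.** None. The article gives no effect size, SD, message count or power for engagement. The size of the problem can only be shown under assumptions.

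**Inputs from the article**

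- Two-sided alpha 0.05.
- Public pilot: "a group of 1000 patients will be recruited on-line (500 patients in the intervention group, and 500 patients in the control group").
- Public non-smokers, from the planning rates 0.07 and 0.14: 500 × 0.07 + 500 × 0.14 = 35 + 70 = 105 of 1000, leaving 895 smokers.
- Clinical pilot: "50 patients in the intervention group, and 50 patients in the control group", so about 50 app users. The planning rates are "expected to be 0.2 and 0.5 in the first and second groups, respectively". Taking 0.5 as the rate in the app arm gives 25 non-smokers and 25 smokers.

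**Assumed inputs, first set.** The read share follows a beta distribution with mean 0.6 and precision 3, so its SD is √(0.6 × 0.4 / 4) = 0.245. Each user receives 30 or 180 messages, the same number for all. The shift in mean is set for about 80% t-test power:

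shift = (1.96 + 0.84) × 0.245 × √(1/n₁ + 1/n₂)

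This gives 0.043 (500 vs 500), 0.071 (895 vs 105) and 0.194 (25 vs 25). There were 1000 replicates per scenario, so the simulation standard error is about 0.013 near a power of 0.80 and 0.007 near 0.05. Chi-square is Pearson without continuity correction.

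| Analysis | Power | Rejection under the null |
|---|---|---|
| t test or Mann-Whitney | 0.78–0.86 | 0.04–0.07 |
| Chi-square, two bands | 0.60–0.68 | 0.05–0.06; 0.06–0.10 with 25 vs 25 |
| Chi-square, four bands | 0.53–0.59 | 0.04–0.06 |
| Chi-square, each distinct ratio, public, 30 messages | 0.19–0.23 | 0.05–0.06 |
| Chi-square, each distinct ratio, public, 180 messages | 0.05–0.07 | 0.03–0.06 |
| Chi-square, each distinct ratio, clinical app users | 0.00–0.11 | 0.00–0.01 |
| Chi-square, messages pooled as read/unread | not meaningful | 0.50–0.80 |

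**Check on the pooled row.** The intraclass correlation is 1/(3 + 1) = 0.25, and the design effect is 1 + (m − 1) × 0.25.

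- m = 30: 8.25, square root 2.87. The true critical distance is 1.96/2.87 = 0.68 standard errors, a two-sided tail of about 0.50.
- m = 180: 45.75, square root 6.76. 1.96/6.76 = 0.29, a tail of about 0.77.

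The simulated values, about 0.50 and 0.77 to 0.80, agree.

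**Assumed inputs, second set.** 500 per public arm, mean ratio 0.45 vs 0.50, SD about 0.25, 400 runs. Approximate t-test power: 0.05 / (0.25 × √(2/500)) = 3.16, and Φ(3.16 − 1.96) = Φ(1.20) = 0.88.

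| Analysis | Power |
|---|---|
| t test or Mann-Whitney | 0.84–0.89 |
| Chi-square, two or four bands | 0.65–0.75 |
| Chi-square, distinct ratios, same count for all (30 / 80 / 180 messages) | 0.30 / 0.16 / 0.09 |
| Chi-square, distinct ratios, count varying by user (around 80 or 180) | 0.00 |

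The last two rows differ because of the number of categories. With exactly 80 messages each there are at most 81 distinct ratios, and about 28% of expected counts fall below 5. With counts varying around 80 there are about 767 distinct ratios among 1000 users, and 99.9% of expected counts fall below 5.

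**The case against.** A reader might infer that the chi-square test has almost no power here and cannot be valid. The article does not support that. Power falls to nil in the public pilot only if every distinct ratio is its own category and message counts vary by user. The article states neither. The word categorical fits a low/high banding at least as well. With pre-set bands the test holds its level in most settings and the loss of power is moderate.

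Three further points deserve weight.

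- **Cut-points are commonly left to a statistical analysis plan, which is not shown.** This stands as far as it goes: missing bands alone would be no finding. But the article does fix a variable type and a test, and both conflict with its own definition.
- **The planned linear regression on all metrics can take the ratio as a number.** So a real relation need not be missed altogether. That regression is an additional joint analysis, however, and it leaves the test assigned to this metric unchanged.
- **Table 2 lists smoking cessation, not trial arm, as the comparison.** A remedy confined to an arm comparison would miss the stated purpose, and it cannot be done in the clinical pilot. An arm comparison in the public pilot still has support, because the Discussion expects engagement to rise.

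**Conclusion.** The point holds as a misclassification: a per-user proportion has been given a test for categories. Every chi-square version examined did worse than the numerical analysis. Banding stays valid but lowers power from 0.78–0.89 to 0.53–0.75. Using each distinct ratio leaves 0.00 to 0.30. Pooling messages gives type I error of 0.50 to 0.80.

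These sizes rest on assumed means, spread and message counts. The ranking of the methods is more secure than any single figure.

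The metric is one of several secondary ones. The sample size and the primary comparison are not affected.

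**What to change.** In the Statistical analysis section, move individual engagement from the chi-square list to the numerical list, and name its comparisons:

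1. **Both pilots, among app users:** compare the ratio between non-smokers and smokers with a t test or Mann-Whitney test, or use a logistic regression of smoking status on the ratio. This is the comparison in Table 2. In the clinical pilot it uses the intervention arm only.
2. **Public pilot only:** compare the ratio between arms with a t test or Mann-Whitney test. The clinical control arm has no app and therefore no ratio.

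If a categorical analysis is really wanted, state the bands before the data are examined and accept the loss of power. Do not pool messages across users in an ordinary chi-square test.

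The cost is a sentence or two of text. No new data are needed and the sample size does not change.

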## Methods

### Design and setting

The primary objective of this study is to assess whether tailored motivational messages supporting smoking cessation—as selected by a health recommender system and delivered by mobile phones to patients—contribute to higher smoking cessation rates.

Secondary objectives include: (1) comparing smoking cessation rates to other user metrics and technical aspects of the system; (2) investigating the relationship between usage of the app used in the 3M4Chan intervention [35] and users’ opinions of messages; and (3) determining if a relation exists between the users’ physical activity levels and their mobile app usage, and their smoking cessation rates.

Both the primary objective and the secondary objectives are common for the clinical and public pilots, although their methodologies and assessments do not completely coincide.

The present document shows the protocol version 1.0.4, 30 May 2018. Major protocol amendments, if any, will be handled by the Taipei Medical University informing any involved stakeholder, and updating the ClinicalTrials.gov registry diligently. Table 1 describes the clincal and public pilot. We followed the Standard Protocol Items: Recommendations for Intervention trials (SPIRIT) guidelines while writing this protocol manuscript (see Additional file 1).

**Table 1 Tab1:** Description of the clinical and public pilot

Name of the pilot	Number of patients	Groups	Treatment	Data to be assessed
Clinical pilot (RCT; 100 patients)	50	Control	Usual care (behavioral therapy and pharmacological treatment)	Smoking cessation rate (clinically validated)
	50	Intervention	Usual care + 3M4Chan app (advanced tailored messages)	Smoking cessation rate (clinically validated)
				Recommender system
				User engagement
				Physical activity
Public pilot (RCT; 1000 patients)	500	Control	m-health (basic tailored messages)	Smoking cessation rate (self-reported)
				Recommender system
				User engagement
				Physical activity
	500	Intervention	m-health (advanced tailored messages)	Smoking cessation rate (self-reported)
				Recommender system
				User engagement
				Physical activity

*RCT* randomized controlled trial

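### Five-star message ratings are assigned a chi-square test and time in the app a t test or ANOVA, so one planned comparison falls under two tests and neither uses the order of the stars

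*Protocol article*

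**What the plan says.** Secondary objective 2, under Design and setting, is "investigating the relationship between usage of the app used in the 3M4Chan intervention [35] and users’ opinions of messages". Two rows of Table 2 serve it directly:

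- User message ratings are "Users’ votes for each message on a 5-star scale". The only comparator listed is user app behavior.
- User app behavior is "Time spent per app section". The comparators listed are message ratings and message satisfaction.

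The Statistical analysis section sorts the secondary metrics by type. App behavior and app usage are among the numerical variables that "will be assessed with *T* tests and variance ANOVA tests". Ratings are among the categorical variables: "user satisfaction with messages, user message ratings, and lifestyle answers to the International Physical Activity Questionnaire (IPAQ)) will be assessed with chi-square tests". The section also plans a linear regression on all metrics combined, and sets two-sided tests at 0.05.

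The section on generating texts adds that a usefulness rating is recorded each time a user receives a message, so one user contributes many votes. For message satisfaction, Table 2 names only a questionnaire, used in the clinical pilot, and gives no response format.

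**The concern.** A Pearson chi-square test treats one to five stars as interchangeable labels. If opinion rises steadily with use, that trend is spread over several degrees of freedom and becomes harder to detect. The test also needs a contingency table, so time in the app would have to be cut into groups, which loses more information. ANOVA of time across the five star levels avoids the grouping but still ignores the order of the levels.

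Both tests can be read as the planned analysis of the same pair of variables, and the text gives no rule for choosing. An analyst could run both and report either. Repeated votes add a second problem: either test assumes independent observations, and votes from one user are unlikely to be independent. At stake is whether secondary objective 2 gets a sensitive and valid answer from data the trial already collects.

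**Working it through.** **No figure to reproduce.** The article powers only the primary outcome. It gives no effect size, power or grouping for the rating-usage comparison, so the sizes below rest on stated assumptions.

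**Inputs from the article.**
- App users: 50 in the clinical pilot (intervention arm only) and 1000 in the public pilot (both arms).
- After the anticipated dropout: 50 × 0.85 = 42.5, about 42; and 1000 × 0.80 = 800.
- Two-sided alpha of 0.05; five rating levels.

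**Assumptions.** One rating value per user; a latent bivariate normal with correlation ρ; the rating cut into five levels; time cut at quantiles into equal groups for the chi-square test.

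**Step 1: cost in degrees of freedom.** Five rating levels by k time groups gives (5 − 1)(k − 1) degrees of freedom: 4, 8 or 12 for k = 2, 3 or 4. A 1-df trend test with 80% power has non-centrality 7.85. With the same non-centrality, power falls to 60%, 47% and 39% on 4, 8 and 12 df. This leaves out the further loss from grouping time.

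**Step 2: simulated power.** There were 1000 runs per row, so the Monte Carlo standard error is at most √(0.25/1000) = 0.016. Rating levels have probabilities 10/20/40/20/10%.

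| n | ρ | Spearman | ANOVA of time across stars | Chi-square, 3 groups | Chi-square, 4 groups |
|---|---|---|---|---|---|
| 42 | 0.4 | 0.68 | 0.48 | 0.22 | 0.19 |
| 50 | 0.3 | 0.51 | 0.36 | 0.17 | 0.15 |
| 50 | 0.4 | 0.75 | 0.57 | 0.29 | 0.27 |
| 800 | 0.10 | 0.72 | 0.54 | 0.34 | 0.32 |
| 1000 | 0.10 | 0.86 | 0.68 | 0.42 | 0.39 |

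In the row n = 50, ρ = 0.4, ANOVA loses 0.75 − 0.57 = 0.18, and chi-square loses 0.75 − 0.29 = 0.46 or 0.75 − 0.27 = 0.48. Over these rows, and the same settings with ratings skewed upward, ANOVA loses about 15-20 points. Over 2 to 5 groups and symmetric, flat or skewed ratings, chi-square loses roughly 25-55 points wherever Spearman has about 45-85% power.

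**Step 3: outside that range.** Chi-square loses about 11-21 points at n = 800-1000 with ρ = 0.05, 14-25 at n = 1000 with ρ = 0.15, 6-14 at n = 50 with ρ = 0.7, and 1-4 at n = 1000 with ρ = 0.2.

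**Step 4: pooled votes with no true association.** Votes share a user random effect with an assumed intra-user correlation of 0.05 to 0.3, and time is unrelated to rating. For chi-square, time is split in two.

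| Votes per user | Type I error, chi-square | Type I error, ANOVA |
|---|---|---|
| 10 | 0.06-0.23 | 0.07-0.25 |
| 30 | 0.12-0.51 | 0.13-0.49 |

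The nominal level is 0.05. The number of votes and the intra-user correlation are assumptions; the article gives neither.

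**The case against.** The strongest reply is that the Statistical analysis section only sorts variables into types and names a test family for each. It nowhere says that ratings will be cross-tabulated against time, or that time will be grouped. Since app behavior is listed as numerical, time could be compared across star levels by ANOVA, and the planned regression could use time in full.

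Much of this stands. A reader might infer that the plan commits to cutting usage into bands and so gives up 30 to 50 points of power. The article does not support that: banding is needed only for the chi-square route, and the size of the loss depends on a correlation that the article does not give. A reader might also infer that satisfaction is an ordered scale compared only with continuous measures. Its format is not given, and one of its listed comparators is the message ratings. Nor does the article say that votes will be pooled as independent; the unit of analysis may be settled in a fuller plan.

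The reply does not remove the problem. Ratings remain assigned to chi-square by name, so having ANOVA available means two tests for one comparison. ANOVA ignores star order as well and, on pooled votes, has the same error inflation. A regression on the combination of all metrics does not say how ratings enter it or how repeated votes are handled.

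**Conclusion.** The point holds in a limited form. An ordered scale is labelled categorical, and its comparison with a continuous measure falls under two tests that both ignore the order. The mid-range losses in the working apply only under the assumed correlations, rating distributions and one value per user. The inflated type I error is conditional on pooling votes, which the article leaves possible but does not state. For satisfaction, the argument about order applies only if the questionnaire is scored on ordered levels. The primary cessation comparison is untouched.

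**What to change.** In the Statistical analysis section, take user message ratings off the chi-square list, and message satisfaction too if it is scored on ordered levels. Name one analysis for the rating-usage comparison, so that it no longer falls under both chi-square and ANOVA. Either of these would serve:

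- Spearman correlation of each user's mean rating with that user's time per app section; or
- an ordinal mixed model on individual votes, with time per section as the predictor and a random effect for user.

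Both use the order of the stars, leave time ungrouped and allow for repeated votes from one user. The change is to wording only and needs no new data or participants. The cost is a slightly more complex analysis than a cross-tabulation, more so for the mixed model than for the correlation.
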